#### 5.4 MAIN OBJECTIVE

The project has two main aims, each with its own main objective.

**Axis 1:** To characterize the sleep of patients undergoing breast cancer treatment before and after adjuvant chemotherapy, compared with patients not treated with chemotherapy and with women free from history of cancer.

**Axis 2:** To explore the regulatory effect of galvanic vestibular stimulation (GVS) on circadian rhythms in patients undergoing treatment for localized breast cancer, compared with SHAM stimulation (not effective).

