## 8 STUDY PLAN

### 8.1 METHODOLOGY

The ICANSLEEP project is a bicentric longitudinal study.

Data from 25 patients with localized breast cancer treated with chemotherapy will be compared with those from a group of 25 patients not treated with chemotherapy and a group of 25 cancer-free volunteers (control groups), matched for sex, age and years of education (Barbizet scale).

The various evaluations will be carried out as follows:

- At T1: Approximately 1.5 months after surgery and before the start of chemotherapy in the CHI group and before the start of radiotherapy in the NCH group,
- At T2: after a delay of around 6 months, within 2 weeks of the end of chemotherapy for the CHI group, or at a distance from radiotherapy for the NCH group,
- At T3: after a two-week intervention with GVS versus non-effective stimulation (known as SHAM). To assess the effect of GVS, patients will be assigned to either the effective GVS group or the SHAM group (random selection). SHAM stimulation involves using the device but receiving a very low-frequency current that has no effect on the vestibular system. This approach has already been used and validated in the COMETE unit (Caen, [name]) with which we collaborate. All cancer-free volunteer participants will undergo GVS.

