## 12 STATISTICAL CONSIDERATIONS

### 12.1 NUMBER OF SUBJECTS REQUIRED

The number of participants in this descriptive and exploratory study is not subject to power calculation. We plan to include 50 breast cancer patients, 25 treated with chemotherapy and 25 not treated with chemotherapy, as well as 25 healthy female volunteers (control group), for a total of 75 participants.

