**Axis 2:** In order to assess the effect of galvanic vestibular stimulation on circadian rhythms, the evolution of circadian rhythm parameters measured by actigraphy during the 2-week intervention (in particular the amplitude and phase of the activity-rest rhythm) will be described by a linear mixed model. The model will include a time effect, an intervention effect (GVS or SHAM) and a time x intervention interaction (parameter of interest to assess whether GVS has an effect on the evolution of circadian rhythm compared with SHAM), and will be adjusted for group (patients or controls) and possibly treatment (chemotherapy or not). To meet secondary objectives, sleep parameters, cortisol levels, cognitive abilities and quality of life assessments will be described before (T2) and after intervention (T3) in each group of patients (GVS or SHAM) and controls (GVS only) and compared pre-post GVS by a McNemar test or a Student (or Wilcoxon) test for paired series. Alternatively, the effect of GVS on sleep, cognitive ability

and quality of life at T3 could be tested in linear or logistic models adjusted for parameters at T2.

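### The Axis 2 main model pools randomised patients with cancer-free women who all receive GVS, so its time x intervention term equals the randomised GVS-versus-SHAM effect in patients only if both groups evolve alike under GVS.

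*Protocol*

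**What the plan says.** Section 5.4 sets the Axis 2 objective as the effect of GVS on circadian rhythms "in patients undergoing treatment for localized breast cancer, compared with SHAM stimulation (not effective"). Cancer-free women are not part of that objective.

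Section 8.1 says that "patients will be assigned to either the effective GVS group or the SHAM group (random selection"), and then that "All cancer-free volunteer participants will undergo GVS". Section 12.2 repeats this for the secondary analyses, where it describes "controls (GVS only"). No control receives SHAM.

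For the main Axis 2 analysis, 12.2 states: "The model will include a time effect, an intervention effect (GVS or SHAM) and a time x intervention interaction". It calls the interaction the "parameter of interest to assess whether GVS has an effect on the evolution of circadian rhythm compared with SHAM", and says the model "will be adjusted for group (patients or controls) and possibly treatment (chemotherapy or not"). Adjusting for patients versus controls makes sense only if controls are in the model. No group x time term is named, and no patients-only main analysis is specified.

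Section 12.1 gives the numbers: "25 treated with chemotherapy and 25 not treated with chemotherapy, as well as 25 healthy female volunteers (control group"). No allocation ratio between GVS and SHAM is stated.

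**The concern.** The parameter of interest compares slopes over the two weeks of stimulation. A main effect for group lets patients and controls start at different levels but makes them share one time trend within each intervention. Because every control is on GVS, the controls' trend enters the GVS slope and has no counterpart on the SHAM side. Randomisation cannot balance this, since controls were never randomised.

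The protocol itself gives reasons to doubt that the trends agree. Section 6 expects circadian rhythms to be altered in patients relative to cancer-free women, and more so after chemotherapy, so controls may have less to resynchronise. Stimulation starts at T2, which for the chemotherapy group falls about two weeks after the last session (8.1, 8.4.4). Controls have no such event.

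What is at stake is whether the trial's only randomised comparison is what its main Axis 2 parameter reports.

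**Working it through.** The protocol gives no alpha, power, effect size or slope SD, so there is no figure of its own to reproduce. The check is on what the named parameter estimates.

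**Inputs**
- 50 patients and 25 controls (12.1); all controls on GVS (8.1).
- Model terms: time, intervention, time x intervention, plus group (12.2). Group is read as a main effect.
- Assumed: 25:25 allocation of patients, with 33:17 and 17:33 (GVS:SHAM) as a range; the same recording days for everyone; equal SD of individual slopes in all groups. Results are in units of that SD.

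**What the term estimates.** With n_G GVS patients and 25 controls:

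interaction = [n_G x slope(GVS patients) + 25 x slope(controls)] / (n_G + 25) − slope(SHAM patients)

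At 25:25 this is 0.5 x slope(GVS patients) + 0.5 x slope(controls) − slope(SHAM patients).

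**Departure from the randomised effect.** The randomised effect is slope(GVS patients) − slope(SHAM patients). Let d = slope(controls) − slope(GVS patients). The difference is then 25/(n_G + 25) x d:

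| GVS:SHAM patients | Weight on d |
|---|---|
| 25:25 | 25/50 = 0.50 |
| 33:17 | 25/58 = 0.43 |
| 17:33 | 25/42 = 0.60 |

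Noise-free fits with 14 time points returned these values. They returned exactly 0 once group x time was added or controls were left out. For example, a true patient effect of 0.5 with flat control slopes (d = −0.5) is estimated as 0.5 − 0.25 = 0.25.

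**Mixed-model check.** Forty simulated data sets with random intercept and slope, no GVS effect and d = 0.75 (outcome units over the two weeks) gave a mean interaction of 0.373 (Monte Carlo SE 0.034), against 0.375 from the formula. With group x time added the mean was 0.05 (SE 0.04), against 0.

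**Precision at 25:25**
- Pooled model: √(1/50 + 1/25) = 0.245.
- Patients only: √(1/25 + 1/25) = 0.283.

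**Illustrative effect on a two-sided 5% test with no GVS effect.** Rejection = Φ(0.5d/0.245 − 1.96) + Φ(−0.5d/0.245 − 1.96):

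| d (slope SD) | Shift 0.5d | Rejection |
|---|---|---|
| 0 | 0 | 5% |
| 0.25 | 0.125 | 8% |
| 0.5 | 0.25 | 17.5% |
| 0.75 | 0.375 | 33% |
| 1.0 | 0.5 | 53% |

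**The favourable case.** With no difference in drift and the same GVS effect in patients and controls, d = 0 and the pooled term is unbiased. Simulated power was then 52% and 90% for effects of 0.5 and 0.8, against 42% and 79% in patients only.

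**The case against.** Four objections deserve an answer.

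*Main effect is an inference.* The text says only that the model is adjusted for group, and exact model terms are often left to an analysis plan that is not shown here. This stands as a caveat. But adjustment ordinarily means a main effect, and 12.2 lists its one interaction explicitly.

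*The bias is conditional.* Its sign and size cannot be read from the protocol. Controls must also have sleep complaints (ISI above 7, section 8.3.3), so they are not obviously unlike patients. This stands too, and it is why the table starts at d = 0 and the favourable case is shown.

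*The study is descriptive and exploratory.* Section 12.1 says so, no alpha is set, and 12.2 speaks of describing the evolution. The rejection rates are therefore illustrations, not breaches of a stated error rate. The label lowers the stakes but does not change what the parameter estimates.

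*Chemotherapy is a different matter.* A reader might infer that the same bias arises because chemotherapy enters only as a possible covariate without a time interaction. The documents do not support this. Patients with and without chemotherapy are all randomised between GVS and SHAM, so leaving out that term causes no systematic bias in the arm contrast. A simulation of 50 patients, unstratified 25:25, no GVS effect and chemotherapy ignored, gave mean estimates of about 0 and rejection of 5.2%, 5.0% and 5.1% for chemotherapy slope shifts of 0, 0.5 and 1.0 SD. Nor does the text support a call for stratified allocation: the group diagrams in section 3 are not available here, and the point about controls does not depend on it.

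**Conclusion.** The point holds for the controls. As written, the Axis 2 parameter of interest mixes the randomised patient contrast with the time trend of a non-randomised group. At an assumed 25:25 split, half of the GVS-side slope comes from that group and the departure is 0.5 x d; the weight runs from 0.43 to 0.60 for splits from 33:17 to 17:33. The conclusion rests on reading the group adjustment as a main effect.

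It would go too far to say that the result will be biased, or biased in a known direction: at d = 0 the pooled term is correct and somewhat more precise. What can be said is that the term matches the objective in 5.4 only under an assumption that the protocol does not state and that its own hypotheses make doubtful. Because the study is declared exploratory and the remedy lies wholly in the analysis, this is a should-fix point.

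**What to change.** Amend the Axis 2 paragraph of 12.2 in one of two ways:
- Estimate the main contrast in the 50 randomised patients only (time, intervention, time x intervention), and describe the controls under GVS separately.
- Keep the controls but add a group x time term, so that time x intervention is identified from patients alone.

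Either recovers the randomised patient contrast exactly in the noise-free fits. A chemotherapy term and its interaction with time may be added for precision; they are optional and correct no bias.

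The change is one sentence and needs no new data, visits or participants. Its price is precision: at 25:25 the standard error of the contrast rises from about 0.245 to 0.283 slope SD (0.283/0.245 = 1.16, about 16%), because the controls no longer contribute to it. The change should be made before the Axis 2 results are seen by arm.

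### As written, the Axis 2 main model puts 25 non-randomised cancer-free women into the GVS slope, so about half of the GVS side of the GVS-versus-SHAM estimate is not randomised

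*Protocol*

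**What the plan says.** Protocol 5.4 sets the Axis 2 main objective as the effect of GVS "on circadian rhythms in patients undergoing treatment for localized breast cancer, compared with SHAM stimulation (not effective"). The population is patients and the comparator is SHAM.

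Protocol 8.1 randomises patients only: "patients will be assigned to either the effective GVS group or the SHAM group (random selection"). The ratio is not given. For the other group it says: "All cancer-free volunteer participants will undergo GVS".

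Protocol 12.1 gives the sizes: "We plan to include 50 breast cancer patients, 25 treated with chemotherapy and 25 not treated with chemotherapy", and "25 healthy female volunteers (control group), for a total of 75 participants". It also says: "The number of participants in this descriptive and exploratory study is not subject to power calculation".

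Protocol 12.2, Axis 2, describes a linear mixed model for the actigraphy rhythm parameters over the two intervention weeks. Its terms are time, intervention (GVS or SHAM) and their interaction, and the interaction is named as the parameter of interest. The model "will be adjusted for group (patients or controls) and possibly treatment (chemotherapy or not"). No other interaction is mentioned, and the model is not limited to randomised women.

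**The concern.** A patients-or-controls covariate has meaning only if controls are in the model. All of them sit in the GVS level of the intervention factor and none in SHAM. Their two-week course therefore feeds the GVS slope, while the SHAM slope comes from patients alone. This is no chance imbalance: it is fixed by design, and randomisation gives no protection against it.

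The protocol itself gives reasons to expect different courses. Section 6 expects patients' rhythms to be altered compared with cancer-free women, and more so with chemotherapy. Section 8.4.4 places T2, where stimulation starts, two weeks after the last chemotherapy session in the chemotherapy group. Spontaneous change over the next two weeks is plausible there and has no counterpart in controls. Depending on its direction, the mixture can create an apparent GVS effect or hide a real one, in the main analysis of the one randomised question in the study.

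**Working it through.** The protocol has no power or sample-size calculation, so there is no stated figure to reproduce.

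**Inputs from the protocol**
- 50 patients and 25 controls (12.1).
- Patients randomised, all controls on GVS (8.1).
- Model terms: time, intervention, time x intervention, group (12.2).

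**Assumptions, not in the protocol**
- 1:1 allocation, so 25 GVS and 25 SHAM patients; 2:1 and 1:2 are also shown.
- Group enters as a main effect.
- Complete data.
- For the illustrations: between-woman slope SD of 1, two-sided 5% test.

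**1. Weights.** The group term absorbs a difference in level. The interaction compares the common GVS slope with the SHAM slope, and with complete data the GVS slope averages over all women on GVS:

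estimate = [25 x slope(GVS patients) + 25 x slope(GVS controls)] / 50 - slope(SHAM patients)
= 0.50 x slope(GVS patients) + 0.50 x slope(GVS controls) - 1.00 x slope(SHAM patients).

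Exact generalised least squares weights for this model gave these values under six variance settings (random intercept alone and with random slopes, with and without intercept-slope correlation), with 2 and with 14 time points. Adding group x time gave 1.00 / 0.00 / -1.00, the randomised contrast.

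**2. Dependence on the ratio.** Controls' share of the GVS slope:
- 33 GVS : 17 SHAM: 25/58 = 43%
- 25 : 25: 25/50 = 50%
- 17 : 33: 25/42 = 60%

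**3. Bias.** If GVS does nothing and the controls' natural slope differs from the patients' by d, the 1:1 estimate is off by d/2.

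**4. Standard error, in slope-SD units.**
- Pooled: sqrt(1/50 + 1/25) = 0.245
- Randomised patients only: sqrt(1/25 + 1/25) = 0.283
- Ratio: 0.283/0.245 = 1.15

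**5. Illustration, no GVS effect.** Simulated per-woman slopes, 25/25/25, pooled-variance test. The variance that mixing two populations adds to the GVS arm is included.

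| Patient-control slope difference (SD) | Bias (SD) | Rejections at nominal 5% |
|---|---|---|
| 0.1 | 0.05 | about 5% |
| 0.25 | 0.125 | about 8% |
| 0.5 | 0.25 | about 16% |
| 0.8 | 0.40 | about 32% to 33% |

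**6. Illustration, GVS shifts patients by 0.8 SD, no natural slope difference.** Power in the randomised patients alone is 79%.

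| Shift in controls under GVS (SD) | Pooled power |
|---|---|
| 0 | about 32% to 33% |
| 0.4 | about 67% |
| 0.8 | about 90% |

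**The case against.** The strongest reply is that 12.2 does not give the form of the group adjustment. If group x time was meant, controls carry no weight in the estimate and the problem disappears. A statistical analysis plan that is not at hand could say so. That is fair as far as it goes. But the protocol does list the model terms and names only one interaction, so the plain reading is a main effect. If more was intended, saying so is the correction.

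The study also calls itself descriptive and exploratory, with no stated alpha or decision rule. Rejection rates and power are therefore a way to show size, not a test of claims the protocol makes. This lowers the stakes. It does not align the estimate with the patient-only objective, and the protocol presents the interaction as its means of judging GVS against SHAM.

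A reader might infer that controls have no disturbance to correct, so dilution is certain. The documents do not support that: controls must also have sleep complaints (ISI above 7) and are matched on age and education (8.1, 8.3.3). Equal courses are not shown either.

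A reader might also infer that the extra precision of pooling is illusory. It is real if patients and controls share the same course and the same response: pooled power is then about 90% against 79%. Nothing in the protocol establishes that condition, and controls without SHAM cannot separate their natural course from their response.

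**Conclusion.** The point holds as a fault in the model as written. Time x intervention does not estimate the randomised effect in patients. At 1:1 allocation, half of the GVS slope comes from women who were not randomised and lie outside the Axis 2 objective. Two assumptions carry this: group is a main effect, and allocation is about 1:1. The second affects only the share, which stays between 43% and 60% over 2:1 to 1:2.

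The size of any bias is unknown, because the protocol gives no slope SD and no expected patient-control difference. The rejection and power figures are illustrations. At a difference of 0.1 SD the error rate is practically nominal; at 0.5 SD and above it is not.

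A reader might extend the point to the optional T3 models adjusted for T2. The protocol does not support that: it gives neither their population nor any covariate beyond the T2 value, so no pooling error is shown there. The separate pre-post descriptions by group serve secondary objectives and do not repair the main model.

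**What to change.** Add one sentence to 12.2, Axis 2. Either fit the main model to the randomised patients only, or keep the controls and add a group x time term so that time x intervention is identified from patients alone. Report the controls' change under GVS descriptively, outside the GVS-versus-SHAM comparison. State the allocation ratio in 8.1.

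No new data are needed. The standard error of the contrast rises by about 15% (0.283 against 0.245 in slope-SD units). That is a real loss of precision only if controls and patients share the same course and the same response to GVS.

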##### Axis 2:

- 1) To evaluate the effects of GVS on:
  - a) Circadian rhythms
  - b) Spatial memory
  - c) The stress-related physiological systems
- 2) To assess the effects of rhythm resynchronization on sleep quality
- 3) To determine whether improved sleep is accompanied by better cognitive performance and quality of life

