## **Axis 2:**

- 1)** GVS would allow :
  - a)** Resynchronizing circadian rhythms (i.e. acrophase) and amplifying the sleep/wake rhythm as the procedure progresses and the cortisol rhythm at the end of the procedure.
  - b)** Improving spatial memory performance compared to T2
  - c)** Reducing hyperactivity of stress-related physiological systems
- 2)** Resynchronizing rhythms improves sleep quality
- 3)** This improvement in sleep quality is associated with better cognitive recovery and quality of life following the course of treatment, compared with the absence of GVS.

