### 12.2 STATISTICAL ANALYSIS

**Axis 1:** In order to characterize the sleep of breast cancer patients before and after adjuvant chemotherapy, sleep parameters measured by polysomnography (in particular sleep efficiency and number of awakenings) or by questionnaire will be described in terms of headcount for qualitative variables, and mean and standard deviation (or median and range) for quantitative variables, at T1 and T2 in each of the groups of interest. Similarly, circadian rhythm parameters measured by actigraphy (e.g. mean amplitude over a week) or by salivary cortisol assay will be described at each time and by group. To assess the effect of cancer on sleep and circadian rhythm, parameters at T1 and T2 will be compared between patients and controls using a Chi test or a Student (or Wilcoxon) test. To assess the effect of chemotherapy on sleep and circadian rhythm, the parameters of chemotherapy-treated patients will be compared between T1 and T2 by a McNemar test or a Student (or Wilcoxon) test for paired series. Alternatively, the effect of chemotherapy on T2 parameters can be tested in linear or logistic models adjusted for T1 parameters. Relationships between sleep parameters and circadian rhythm parameters will be assessed using a correlation matrix (Pearson's or Spearman's). The relationship between sleep parameters and scores on cognitive tests and quality-of-life assessments can be assessed at any time using a linear mixed model (taking into account correlation between repeated measures of the same subject).

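### Axis 2 secondary objectives 2 and 3 ask how changes in rhythm, sleep, cognition and quality of life go together, but the analyses assigned to them take one outcome at a time and relate no change to another.

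*Protocol*

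**What the plan says.** Protocol section 5.5 lists three Axis 2 secondary objectives. The first concerns effects of GVS. The second is "To assess the effects of rhythm resynchronization on sleep quality", and the third is "To determine whether improved sleep is accompanied by better cognitive performance and quality of life". Section 6 restates these as hypotheses: "Resynchronizing rhythms improves sleep quality", and "This improvement in sleep quality is associated with better cognitive recovery and quality of life". The sentence containing that last quote goes on to set the improvement against not receiving GVS.

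The Axis 2 paragraph of section 12.2 gives the method: "To meet secondary objectives, sleep parameters, cortisol levels, cognitive abilities and quality of life assessments will be described before (T2) and after intervention (T3"). These measures are then to be "compared pre-post GVS by a McNemar test or a Student (or Wilcoxon) test for paired series". As an alternative, a GVS effect on each such measure may be examined in a T3 model; the sentence on this ends with the words "and quality of life at T3 could be tested in linear or logistic models adjusted for parameters at T2".

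The Axis 1 paragraph of the same section contains two association methods. Sleep and rhythm parameters are to be related by a correlation matrix. For cognition and quality of life, "The relationship between sleep parameters and scores on cognitive tests and quality-of-life assessments can be assessed at any time using a linear mixed model".

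**The concern.** Objectives 2 and 3 are about pairs of outcomes, and the analysis assigned to them sees one outcome at a time. A paired T2-T3 test asks whether one mean moved. The T2-adjusted T3 model asks whether GVS moved one outcome. Neither contains both rhythm and sleep, or both sleep and cognition.

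Two wrong conclusions then become possible. If sleep and cognition both improve on average for unrelated reasons, two significant tests invite the statement that better sleep was accompanied by better cognition. Such reasons are plausible here: in the chemotherapy group T2 falls about two weeks after the last session (8.4.4), and the cognitive battery is taken for the third time at T3 (8.4.5). Conversely, if women whose sleep improves do gain in cognition but the averages stay put, the plan reports nothing. In both cases the proposed chain from GVS to rhythm to sleep to cognition and quality of life is left untested.

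**Working it through.** **1. What each analysis can address**

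| Analysis in 12.2 | Quantity tested | Both outcomes of a pair in one analysis? | Uses T2-T3 changes? |
|---|---|---|---|
| Paired test (Axis 2) | mean change of one outcome | no | yes |
| T3 model adjusted for T2 (Axis 2) | GVS effect on one outcome | no | in effect, yes |
| Correlation matrix (Axis 1) | sleep with rhythm | yes | not stated; levels |
| Mixed model (Axis 1, optional) | sleep with cognition and quality of life | yes | not stated; levels |

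No row has a yes in both of the last two columns. Table 2 in section 7.2 supports reading objectives 2 and 3 as links: objective 2 lists actigraphic rhythm together with the sleep measures, and objective 3 lists the sleep measures together with neuropsychological and quality-of-life scores.

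**2. Inputs for the size**

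Section 12.1 plans 50 patients and 25 controls without a power calculation, so there is no figure to reproduce. Section 8.1 randomises patients to GVS or SHAM without giving a ratio. Assumed: 1:1 allocation (25 GVS patients), two-sided alpha 0.05, bivariate normal changes with SD 1, and the mean shifts and correlations below.

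**3. No link, but both means shift by 0.5 SD (n = 25)**

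Paired t test: noncentrality 0.5 × √25 = 2.5, 24 df, critical value 2.064, power 0.67. With unrelated changes both tests reject with probability 0.67 × 0.67 ≈ 0.45 (simulation, 20,000 replicates: 0.671, 0.675, both 0.450). With 50 women, single 0.93 and both 0.87. The test of the correlation of changes rejects in about 5%.

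**4. A link, but no mean shift**

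Each paired test rejects in about 5%, and both in about 1%. Power of the correlation test is approximately Φ(atanh(ρ)·√(n − 3) − 1.96):
- ρ = 0.5, n = 25: 0.549 × 4.690 = 2.58, giving Φ(0.62) = 0.73 (simulation 0.75).
- ρ = 0.6, n = 25: 0.693 × 4.690 = 3.25, giving Φ(1.29) = 0.90 (simulation 0.91).
- ρ = 0.5, n = 50: 0.549 × 6.856 = 3.77, giving Φ(1.81) = 0.96 (simulation 0.97).

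**5. The T2-adjusted alternative**

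Approximated by comparing changes in 25 GVS against 25 SHAM patients. Arm effect 0.8 SD on both outcomes, no link: noncentrality 0.8 × √(25/2) = 2.83, power 0.79 each, both 0.79 × 0.79 ≈ 0.63. With correlation 0.5 to 0.6 and no arm effect, about 5% each and about 1% both.

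**6. The mixed model on levels**

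Fifty women, T2 and T3, intraclass correlation 0.6, changes unrelated. With a between-woman correlation of 0.5 the model rejects in about 50% of data sets; with 0.3, in about a quarter. Habitually poor sleepers who also score worse are enough to produce this. The within-woman sleep term and the regression of change on change both stay near 5%. With a within-woman correlation of 0.5, each has about 95% power.

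**7. Limits of a change-on-change analysis**

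If measurement noise halves a correlation of 0.5 to 0.25: n = 25, 0.255 × 4.690 = 1.20, power 0.22 (simulation 0.23); n = 50, 0.255 × 6.856 = 1.75, power 0.42. If GVS shifts both outcomes by 0.8 SD in every woman with no residual correlation, the arm-adjusted slope rejects in only about 5%.

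**The case against.** The strongest reply has four parts.

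*The hypotheses are partly arm comparisons.* The sentence stating hypothesis 3 ends with a comparison against no GVS, and the T2-adjusted T3 model addresses that part. This stands, so the arm comparison should be kept rather than replaced. It would also be wrong to infer that the plan offers nothing beyond mean change from T2 to T3: the adjusted model is there. It still does not connect one outcome with another.

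*Section 12.2 already has association methods.* The correlation matrix is a firm commitment, and the mixed model's timing, read generously, reaches T3. But both stand under Axis 1, neither is stated for T2-T3 changes, and the mixed model is optional. How a model is parameterised can be left to a statistical analysis plan. The mismatch here lies in the protocol's own text, which says how the secondary objectives are met and names analyses that do not meet two of them.

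*The 67% is not an error rate.* This is right. It is ordinary power of a test valid for its own null. A reader might infer that the paired tests have an inflated type I error; they do not. The fault arises only when their result is read as an answer to objective 2 or 3.

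*A change-on-change regression has its own gaps.* It discards the randomised part of the effect and suffers from noisy change scores. Moreover, a signed acrophase change need not measure resynchronisation, since either an advance or a delay could be the correction. All three points stand and shape the remedy.

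**Conclusion.** The point holds: objectives 2 and 3 of Axis 2 concern linked changes, and no analysis that section 12.2 assigns to them relates one change to another. Under the assumptions above, both single-outcome tests can be significant in about 45% of trials (25 women) when no link exists, and each rejects in about 5% when a link exists without a mean shift.

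These figures illustrate the mismatch and are not forecasts. They rest on assumed effect sizes, correlations, intraclass correlation and 1:1 allocation, none of which the protocol gives. The weight is moderate: section 12.1 calls the study descriptive and exploratory, these are secondary objectives, and the primary Axis 2 model is unaffected. A reader might also infer that adding the regressions would establish the causal chain. It would not, because only GVS is randomised; rhythm and sleep changes are not.

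**What to change.** In the Axis 2 paragraph of section 12.2:

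- Keep the T2-adjusted comparison of each outcome, stated as GVS versus SHAM in the randomised patients. It serves the part of hypothesis 3 that refers to not receiving GVS, and it captures a uniform GVS effect, which the slopes below do not.
- Add for objective 2 a regression of the T2-T3 change in sleep on the change in rhythm. Add for objective 3 a regression of the change in cognition and in quality of life on the change in sleep. Adjust both for arm and chemotherapy group.
- Report slopes with 95% confidence intervals and describe them as exploratory associations.
- For acrophase, prespecify a measure of resynchronisation in place of the signed change.
- If the mixed model is used for objective 3, separate within-woman from between-woman sleep and base the conclusion on the within-woman term.

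The cost is a few sentences and some regressions on data already collected; no visits, measures or participants are added. The drawback is precision: change scores based on a single polysomnography night at each time are noisy, so slopes will be attenuated and a null result should be read from its interval.
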